### Statistical analysis

#### Sample size calculation

The power calculation is based on expected differences in SF-36 z-scores. Based on our own comparison of type 2 diabetes patients with mainly untreated depression versus non-depressed patients, we assume differences of δ = 0.6 between CBT and TAU and of δ = 0.4 between CBT and SH. For the latter comparison, a significant difference can be detected with a power of 90% if n = 132 patients per intervention group are enrolled (2-sided t-test, α = 0.05). Given 132 patients in the CBT group, it is sufficient to enroll 51 patients in the TAU group to achieve a power of 95% for the comparison CBT vs. TAU. We therefore plan to recruit a total number of 315 patients (132 in CBT, 132 in SH, and 51 in TAU). We expect a rate of loss to follow-up of 20% in light of our experiences in the ongoing Depression and Diabetes (DAD) study and assuming that mortality will play a role in our sample because of the age of the patients. Analyses will be performed using an intent-to-treat principle (ITT) that includes all randomised subjects in the groups to which they were assigned. The last observation carried forward method (LOCF) will be used for the handling of missing data due to dropouts. The primary population for analysis is the ITT population. To fully appreciate the potential influences of missing responses and the LOCF method chosen as imputation procedure, additional sensitivity analyses examining the effects of different imputation methods will be performed and discussed.

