### Trial sample

A total of 315 subjects will be included in the trial. Patients will be recruited in approximately 20 centres that specialise in diabetes treatment in the Rhine-Main and Ruhr areas. In the participating centres, all 65- to 85-year-old patients with type 2 diabetes who give informed consent will be screened in a two-stage procedure (Patient Health Questionnaire (PHQ-9) [30] followed by the Structured Clinical Interview for DSM IV Disorders (SCID) [31]. All patients with minor depression or mild major depression will be included in the trial. Other inclusion and exclusion criteria of the trial are listed below.

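### The expected 20% loss to follow-up is not reflected in the 315 patients or in the printed 90% and 95% power, so those figures are not supported as stated

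*Protocol article*

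**What the plan says.** All the inputs are in the protocol article, under Sample size calculation.

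- Scale and effects: "The power calculation is based on expected differences in SF-36 z-scores", and "we assume differences of δ = 0.6 between CBT and TAU and of δ = 0.4 between CBT and SH".
- Test: "2-sided t-test, α = 0.05".
- CBT vs SH: a difference "can be detected with a power of 90% if n = 132 patients per intervention group are enrolled".
- CBT vs TAU: with 132 in CBT, "it is sufficient to enroll 51 patients in the TAU group to achieve a power of 95% for the comparison CBT vs. TAU".
- Total: 132 + 132 + 51 = 315. The Trial sample section repeats it: "A total of 315 subjects will be included in the trial".
- Loss: "We expect a rate of loss to follow-up of 20" per cent, with mortality named as one contributor.
- Analysis: intention to treat on all randomised patients, with LOCF for dropouts and sensitivity analyses using other imputation methods. Under Analysis of outcome variables, the primary model regresses the one-year z-score on intervention and baseline score.

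The paragraph does not say that 132/132/51 already allows for the loss, or that LOCF or baseline adjustment is the reason no allowance was made.

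**The concern.** The paragraph gives a power calculation, a total and a loss rate together, but the loss rate enters neither of the other two. If the sizes are those for complete follow-up, the printed power describes a trial with no dropouts, which the authors do not expect to run. CBT vs TAU is the primary hypothesis. A reader of a non-significant result there would assume a 5% risk of having missed a true difference of 0.6, when the risk could be nearer 10%. The point applies to each contrast's stand-alone power and does not depend on the hierarchical testing order.

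**Working it through.** **Inputs.** Differences 0.6 (CBT vs TAU) and 0.4 (CBT vs SH), two-sided α = 0.05, sizes 132/132/51 and loss 20%, all from Sample size calculation. The SD is not printed. SD = 1 is assumed, as the z-scale implies, and the next step supports it.

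**Method.** Power of a two-sample t-test from the noncentral t distribution, with n1 + n2 − 2 degrees of freedom and noncentrality δ / (SD·√(1/n1 + 1/n2)).

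**Step 1: reproduce the plan, with no loss.**

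- CBT vs SH: the normal formula gives n = 2(1.960 + 1.282)²/0.4² ≈ 131.4, so 132 per group. At 132/132 the noncentrality is 0.4/√(2/132) = 3.25 and the power is 89.9%.
- CBT vs TAU: at 132/51 the noncentrality is 0.6/√(1/132 + 1/51) = 3.64 and the power is 95.2%. With 50 in TAU it is 94.9%, so 51 is the smallest number that reaches 95%.

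Both printed figures reproduce with zero dropout and no slack.

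**Step 2: apply the 20% loss on the stated t-test.** 0.8 × 132 = 105.6 and 0.8 × 51 = 40.8, so about 106/106/41 (253 in all) have one-year data.

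- CBT vs TAU, 106/41 at 0.6: noncentrality 3.26, power 90.0%.
- CBT vs SH, 106/106 at 0.4: noncentrality 2.91, power 82.6%.

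Rounding down to 105/105/40 gives 89.4% and 82.2%.

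**Step 3: the planned LOCF on all 315, still unadjusted.** If dropouts retain a fraction f of the effect, the expected difference is δ × (0.8 + 0.2f). n stays at 132/132/51 and the SD is held at 1.

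| Effect retained by dropouts | Differences (TAU; SH) | Power CBT vs TAU | Power CBT vs SH |
|---|---|---|---|
| all | 0.60; 0.40 | 95.2% | 89.9% |
| 75% | 0.57; 0.38 | 93.0% | 86.8% |
| 50% | 0.54; 0.36 | 90.3% | 83.0% |
| none | 0.48; 0.32 | 82.5% | 73.6% |

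**Step 4: what baseline adjustment could recover.** With correlation r between the baseline score and the analysed score, the residual SD is taken as √(1 − r²).

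| Basis | r | Power CBT vs TAU | Power CBT vs SH |
|---|---|---|---|
| Observed 106/106/41, full effect | 0.45 | 95.2% | 90.1% |
| LOCF, 75% retained | 0.30 | 95.0% | 89.7% |
| LOCF, 50% retained | 0.45 | 95.4% | 90.4% |
| LOCF, none retained | 0.45 | 90.0% | 82.7% |
| LOCF, none retained | 0.60 | 95.2% | 89.9% |

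The correlation needed therefore depends on how much effect the dropouts keep. A value of r alone does not settle the matter.

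**The case against.** The strongest reply is that the 90% and 83% describe an analysis the trial will not run. All 315 patients are analysed under intention to treat with LOCF, and the model adjusts for baseline. On that analysis the printed power may well be reached: half the effect retained with r = 0.45 gives 95.4% and 90.4%. This stands. It means the article cannot be said to miss its power, only that it has not shown that it reaches it. It does not remove the point, because the printed calculation is an unadjusted t-test, no correlation or retained effect is given, and LOCF is not offered as the reason for making no allowance. LOCF keeps the number analysed, but it keeps the full difference only if the carried-forward scores already show it.

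A reader might infer three stronger things that the document does not support.

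- *The primary contrast carries a miss risk of about 17%* (100 − 82.5). That needs every dropout to contribute no effect. Table 1 schedules the SF-36 at months 3, 6, 9, 12 and 15, and month 3 falls at about the end of the 12 weekly sessions. Only patients lost before month 3 would necessarily carry a baseline score, so this is an extreme case.
- *The trial is underpowered.* On the stated t-test with 20% loss, the primary contrast keeps about 90% and the second about 83%.
- *The trial must recruit more.* Full inflation would give 132/0.8 = 165 twice and 51/0.8 = 63.75, rounded up to 64: 394 in all, 79 more than planned. That is one way to restore the printed figures on an unadjusted completer test, but the planned analysis may not need it.

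**Conclusion.** The point holds in a limited form. The sizes 132/132/51 are those for complete follow-up, and the 20% loss expected in the same paragraph changes neither the total nor the power. Each printed sum and power reproduces; the fault is an allowance that is stated but not applied. On the article's own t-test the shortfall is about 5 percentage points for CBT vs TAU (95% to 90%) and 7 for CBT vs SH (90% to 83%). LOCF with half the effect retained gives nearly the same figures. With 75% retained, the shortfall is about 2 to 3 points.

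These results assume SD = 1, equal 20% loss in every arm and, for LOCF, an unchanged SD and the same retained fraction in both contrasts. The true power under the planned analysis depends on the retained effect and the baseline correlation. The article gives neither, so the printed power is unsupported as stated rather than shown to be wrong. The design does not have to change.

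**What to change.** Keep 315. Under Sample size calculation, say that 90% and 95% apply without loss to follow-up. Then restate the power with 20% loss: about 83% for CBT vs SH and 90% for CBT vs TAU on the unadjusted t-test. Say that this follows either from about 106/106/41 patients with one-year data or from LOCF on all 315 with half the effect retained, so that the statement does not suggest a completer analysis.

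If the sponsor prefers to keep 90% and 95%, state both assumptions that they need under the planned LOCF, baseline-adjusted analysis: the share of the effect that dropouts retain, and the correlation between baseline and one-year MCS. Half retained with r of about 0.45, or none retained with r of about 0.60, would do. A correlation on its own is not enough, because 0.45 with no effect retained gives only 90.0% and 82.7%.

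The cost is a sentence or two and no extra patients. The stated power becomes slightly less favourable, or it rests on assumptions that readers can see.

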#### Analysis of outcome variables

There will be one analysis of depression and health related quality of life after completion of the trial, i.e. no interim analyses are planned for the primary parameters. The primary response variable is the z-transformed SF-36 Mental Component Summary (MCS) score at the one-year follow-up. We plan to employ a linear regression model of z-transformed SF-36 score on type of intervention and baseline score. Additional variables (e.g. gender, age, centre, and illness severity) may be included in the model, if indicated.

The hypotheses will be ordered hierarchically (1: CBT vs. TAU, 2: CBT vs. SH); the second hypothesis will be tested at a two-sided 5% level only if the first test is significant at a two-sided 5% level. Analyses will be performed using an intent-to-treat analysis, and the last observation carried forward method will be used for the handling of missing data. Secondary outcomes (HRQoL (physical component), severity of depression, prophylaxis of moderate/severe major depression, glycaemic control (HbA1c), and mortality) will be analysed primarily in a descriptive manner. For binary response variables, the numbers and proportion of responders will be presented together with 95% confidence intervals for the proportions; continuous variables will be analysed by use of summary statistics. If differences between intervention groups are investigated, outcomes will be adjusted for baseline values through use of appropriate models (linear, logistic, or Poisson regression); however, the p-values for such secondary analyses may not be interpreted as confirmatory findings. Subgroup analyses stratified for gender (male/female), mild cognitive impairment (yes/no), and number of previous depressive episodes (<3, ≥3) also will be carried out. These analyses will be conducted using the same methods as those for the full population. Time to onset of moderate/severe major depression and conversion rates to dementia will be analysed using Kaplan-Maier estimates.

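### The recruitment targets of 132/132/51 are complete-data numbers, so the stated 90% and 95% power make no allowance for the 20% loss that the plan expects

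*Protocol article*

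**What the plan says.** Under Sample size calculation, the article gives the scale ("The power calculation is based on expected differences in SF-36 z-scores"), the effects ("we assume differences of δ = 0.6 between CBT and TAU and of δ = 0.4 between CBT and SH") and the test ("2-sided t-test, α = 0.05"). For CBT vs SH it concludes that "a significant difference can be detected with a power of 90% if n = 132 patients per intervention group are enrolled". For the other comparison, given 132 in CBT, "it is sufficient to enroll 51 patients in the TAU group to achieve a power of 95% for the comparison CBT vs. TAU". It derives the recruitment total of 315 directly from these numbers, and Trial sample repeats 315 as the number to be included.

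The next statement is "We expect a rate of loss to follow-up of 20" per cent, justified by experience in an ongoing study and by expected deaths in an elderly sample. No group size is raised and no lower power is given. The text then moves to intention-to-treat with LOCF and promises sensitivity analyses with other imputation methods. It does not say that LOCF is meant to offset the loss in the power calculation.

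Under Analysis of outcome variables, the primary model is a linear regression on intervention and baseline score. CBT vs TAU is tested first and CBT vs SH second: "the second hypothesis will be tested at a two-sided 5% level only if the first test is significant".

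**The concern.** A recruitment target normally has to exceed the number needed for analysis when loss is expected. Here the two are the same, although a loss rate is quoted in the same paragraph. Either the loss costs power, or something in the analysis is assumed to make it good. The article does neither calculation.

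At stake is the power claimed for both hierarchically tested comparisons. The exposure is greater for CBT vs SH, which set the 132 per group and is meant to show that CBT does more than a group setting alone. A reader of a non-significant result there would judge it against a 90% that the stated inputs do not support once 20% are lost.

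**Working it through.** **Inputs.** From Sample size calculation: two-sided α = 0.05, t-test, δ = 0.4 (CBT vs SH) and 0.6 (CBT vs TAU), groups of 132/132/51, loss 20%. The SD is not stated. I assume 1, which the z-score scale implies and which reproduces both stated figures.

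**Formula.** Noncentrality λ = δ / (SD × √(1/n₁ + 1/n₂)), with n₁ + n₂ − 2 degrees of freedom. Power is the probability that a noncentral t variable with this λ exceeds the two-sided 5% critical value in absolute size.

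**Step 1: reproduce the plan with no loss.**
- Normal approximation for δ = 0.4 and 90% power: n = 2 × (1.960 + 1.282)² / 0.4² = 131.3, so 132 per group.
- 132 vs 132, δ = 0.4: λ = 3.25, power 89.9% (normal approximation 90.1%).
- 132 vs 51, δ = 0.6: λ = 3.64, power 95.2%. With 50 in TAU it is 94.9%, so by the t-test 51 is the smallest TAU group that reaches 95%.

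The stated figures are therefore complete-data figures. If 132 already contained an allowance for loss, 80% of it (106) would have to give 90%. Step 2 shows that it does not.

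**Step 2: the plan's t-test on the patients observed after 20% loss.** 0.8 × 132 = 105.6 and 0.8 × 51 = 40.8, so about 106/106/41.
- 106 vs 106, δ = 0.4: λ = 2.91, power 82.6%. Type II error is 17.4% instead of 10.1%.
- 106 vs 41, δ = 0.6: λ = 3.26, power 90.0%. Type II error is 10.0% instead of 4.8%.

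**Step 3: all 315 kept by LOCF.** Let s be the share of the one-year effect that the carried-forward values hold. The documents do not give s, so it is varied; SD stays at 1. The average effect becomes δ × (1 − 0.20 × (1 − s)), analysed on 132/132/51.

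| s | δ, CBT vs SH | Power | δ, CBT vs TAU | Power |
|---|---|---|---|---|
| 0 | 0.32 | 73.6% | 0.48 | 82.5% |
| 0.5 | 0.36 | 83.0% | 0.54 | 90.3% |
| 0.75 | 0.38 | 86.8% | 0.57 | 93.0% |
| 1 | 0.40 | 89.9% | 0.60 | 95.2% |

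**Step 4: baseline adjustment on 106/106/41.** With a baseline-to-follow-up correlation r (also not in the documents), the residual SD is √(1 − r²).

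| r | CBT vs SH | CBT vs TAU |
|---|---|---|
| 0 | 82.6% | 90.0% |
| 0.3 | 86.0% | 92.5% |
| 0.4 | 88.5% | 94.2% |
| 0.5 | 91.7% | 96.3% |

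Both stated figures are restored from about r = 0.45.

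**Step 5: for scale.** Full inflation would be 132/0.8 = 165, again 165, and 51/0.8 = 63.75, so 64. The total is 394, or 79 more than 315.

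**The case against.** The strongest reply is that the 83% and 90% belong to a complete-case, unadjusted analysis that the plan does not make primary. The plan analyses everyone randomised, with LOCF, and adjusts for baseline. Table 1 schedules the SF-36 at baseline and at months 3, 6, 9, 12 and 15, and month 3 falls at about the end of the 12 weekly sessions. Only patients lost before then would have nothing but a baseline value to carry forward, so s = 0 is a worst case. Modest help from both sources nearly closes the gap: s = 0.75 with r = 0.3 gives 89.7% and 95.0%.

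This stands as a limit on certainty. A reader might infer that the trial will certainly fall short of 90% and 95%. The documents do not support that, because neither s nor r is known and either could recover the loss. The reply does not justify the paragraph as written, however. The power there rests on an unadjusted t-test, claims no gain from baseline adjustment, and does not argue that dropouts' last values hold the full effect.

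A reader might also infer that the 90% for CBT vs SH is wrong because that test is run only after a significant CBT vs TAU result. It is not wrong. The article quotes power for each comparison on its own, which is a legitimate figure, and it discloses the order of testing. The chance of passing both tests is about 87% with no loss and 77% with loss (bivariate normal, correlation 0.37 through the shared CBT group). That is useful information, not a correction.

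**Conclusion.** The point holds as an omitted allowance. The numbers 132, 51 and 315 are computed correctly for complete data, but the power attached to them is not reconciled with the 20% loss stated beside them. On the plan's own unadjusted basis (SD 1, equal loss in all groups), power is about 83% instead of 90% for CBT vs SH and about 90% instead of 95% for CBT vs TAU. With LOCF it lies between 73.6% and 89.9%, and between 82.5% and 95.2%, depending on the assumed share of the effect carried forward. The stated values hold only at the top of those ranges or with a sufficient, unstated baseline correlation.

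It would go too far to call the trial underpowered. The primary comparison, CBT vs TAU, keeps about 90% even on the complete-case basis, and type I error and the planned analysis are untouched. The larger shortfall is in the second test. This is a statement to correct, not a flaw that threatens the trial.

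**What to change.** Keep 315 and revise the paragraph:

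1. Say that 132/132/51 are the numbers required with complete data, and that SD = 1 is assumed.
2. Restate the power under 20% loss as about 83% (CBT vs SH) and 90% (CBT vs TAU) on the unadjusted t-test basis.
3. Show the LOCF range beside it for carried-forward shares of none, half and all, labelled as assumptions.
4. Claim recovery from baseline adjustment only with a stated baseline-to-follow-up correlation and its source, for example the sponsor's own earlier data.

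Adding the joint power through the hierarchy is optional.

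The cost is the rewording of one paragraph and less favourable figures in print. No extra patients are needed. Holding 90% and 95% on observed data without relying on adjustment would instead take 394 patients.

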Depression has a strong impact not only on medical outcomes in diabetes but also on psychological and social outcomes [15,16]; therefore, the treatment of comorbid depression is increasingly considered essential for the clinical care of diabetes patients [17]. The described summary of the evidence for randomised controlled trials (RCT) treatments for depression in diabetes was based on a PubMed search. Eleven trials addressed the treatment of depressed diabetes patients in RCTs and were classified according to the studied interventions [18]. Counselling [19] and cognitive behavioural therapy (CBT) [20] demonstrated positive results in two trials; however, generalisability was restricted due to methodological limitations (small sample sizes, six-months follow-up, one trial site, and CBT not specific for diabetes). The most recent trial, which evaluated supportive psychotherapy, showed moderate improvement in depression according to post-treatment evaluation but not follow-up data [21]. Three RCTs [22-24] showed that antidepressants were superior to placebo in treating full-blown major depression. In the only RCT involving older, mildly depressed diabetes patients, paroxetine demonstrated no statistically significant differences compared with placebo therapy regarding health related quality of life (HRQoL), glycaemic control, or symptoms of depression after six months [25]. The effectiveness of algorithm-based, flexible interventions using a combination of psychological and pharmacological treatments compared with standard care was evaluated in four RCTs. The psychological modules of these treatments included problem-solving training [26,27], counselling [28], and interpersonal therapy [29]. Antidepressants were given according to the patients' preferences or following a predefined treatment algorithm. Three trials [25-27] provided evidence of successful treatment of depression. An additional RCT, which included elderly depressed diabetes patients (among others), showed that patients in the mixed treatment condition were less likely to die over the course of a five year interval than patients treated with usual care (adjusted hazard ratio 0.49, 95% CI [0.24, 0.98]) [28]. The mixed approaches provide at present the best available scientific evidence of successful treatment of depression.

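### LOCF is the primary missing-data method for the one-year SF-36 mental score, so the confirmatory contrast is biased if the treatment difference changes over time or dropout differs by arm

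*Protocol article*

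**What the plan says.** The Sample size calculation section of the protocol article sets the rule: "The last observation carried forward method (LOCF) will be used for the handling of missing data due to dropouts". The primary population is intention-to-treat and "includes all randomised subjects in the groups to which they were assigned". The section Analysis of outcome variables repeats the rule straight after the hierarchical test: "the last observation carried forward method will be used for the handling of missing data".

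The endpoint is one time point: "The primary response variable is the z-transformed SF-36 Mental Component Summary (MCS) score at the one-year follow-up". The model uses no intermediate visit: "We plan to employ a linear regression model of z-transformed SF-36 score on type of intervention and baseline score", with further covariates only if indicated. CBT versus TAU is tested first, and CBT versus SH only if the first test is significant.

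On attrition the article says "We expect a rate of loss to follow-up of 20" per cent, in part "assuming that mortality will play a role in our sample because of the age of the patients". It acknowledges that LOCF may influence the result and promises sensitivity analyses with other imputation methods, without naming any.

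Table 1 marks the SF-36/EQ-5D row at baseline and at Months 3, 6, 9, 12 and 15. Sessions are weekly for 12 weeks and monthly for 12 further months (Trial design).

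**The concern.** The primary hypothesis is about benefit at one year, well after the weekly phase ends. LOCF replaces a missing one-year score with whatever was last recorded. That may be a baseline score, the score at the end of weekly therapy, or a late score from Month 9 or 12. Each substitution is right only if the patient would not have changed afterwards.

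The design gives reason to doubt that. Treatment intensity falls after week 12, and the Background describes a trial of supportive psychotherapy that "showed moderate improvement in depression according to post-treatment evaluation but not follow-up data". If a difference fades, LOCF overstates the one-year effect. If it builds up, or if patients leave before any post-baseline score, LOCF understates it. If both arms change equally but one loses more patients, LOCF creates a difference where none exists.

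The LOCF p-value decides the first hypothesis and whether the second is tested, so both confirmatory claims are exposed.

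**Working it through.** **Inputs from the article.** Planned allocation is CBT 132, SH 132, TAU 51. Assumed differences are 0.6 (CBT vs TAU) and 0.4 (CBT vs SH). The test is a two-sided t-test at 0.05, and expected loss is 20%. **Assumptions.** The SD is 1 (none is stated; the outcome is a z-score). The one-year visit is taken as Month 15, that is 12 weeks plus 12 months. All trajectories, correlations and arm-specific dropout rates below are illustrative.

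**1. The plan's own figures.** Noncentral-t power is 89.9% for 132 vs 132 at 0.4 and 95.2% for 132 vs 51 at 0.6. The stated 90% and 95% reproduce with no missing data.

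**2. Values affected.** 0.20 × 315 = 63.

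**3. Expected LOCF contrast with equal dropout.**
E = 0.8 × (one-year difference) + 0.2 × (difference at the visit carried forward).

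- All dropouts leave after Month 3, difference 0.6 there and 0 at one year: 0.8 × 0 + 0.2 × 0.6 = 0.12. Noncentrality is 0.12 × √(132 × 51/183) = 0.12 × 6.07 = 0.73, so two-sided rejection is 11.2%.
- Same, with a true one-year difference of 0.2: 0.8 × 0.2 + 0.2 × 0.6 = 0.28.
- All dropouts leave before Month 3 (baseline carried, expected difference 0): 0.8 × 0.6 = 0.48 for CBT vs TAU and 0.8 × 0.4 = 0.32 for CBT vs SH.

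**4. Dropout spread over visits.** This was simulated with 132 vs 51, 4000 runs per scenario, correlation 0.5 + 0.5 × 0.8^lag, monotone dropout missing at random, and the baseline-adjusted model. The comparison is a sequential-regression estimate that uses every visit and approximates a likelihood analysis.

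| Scenario (dropout CBT/TAU) | True | LOCF | All visits |
|---|---|---|---|
| 0.6 at Month 3, fading to 0 (21%/21%) | 0 | 0.064, rejects 7.9% | 0.002 |
| Both arms improve by 0.6 (10%/31%) | 0 | 0.092, rejects 11.5% | 0.001 |
| Difference builds up to 0.6 (21%/21%) | 0.6 | 0.526 | 0.604 |
| 0.6 from Month 3 onward (21%/21%) | 0.6 | 0.575 | 0.603 |

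Hand check of the first row: the last visit seen is roughly equally often baseline, Month 3, 6, 9 or 12. The mean carried difference is (0 + 0.6 + 0.45 + 0.3 + 0.15)/5 = 0.30, and 0.208 × 0.30 = 0.062.

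**5. No true difference, unequal dropout.** Bias = (difference in dropout rates) × (common change after the carried visit). With 10% vs 30% and a change of 0.3 to 1.0 SD, bias is 0.06 to 0.20. Type I error is then 6.5% to 22.6% for CBT vs TAU. With equal dropout and equal change in both arms, bias is 0.

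**The case against.** The strongest defence is that the article recognises the influence of LOCF and commits to sensitivity analyses. That is to its credit, but no method is named and the confirmatory p-value stays with LOCF. The other objections have more force.

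- **Fading is not established.** The 0.12 case needs every dropout just after Month 3 and complete loss of effect. Monthly sessions continue for a year, and the trial cited in the Background tested supportive psychotherapy on a depression outcome. A reader might infer that LOCF favours CBT here; the document does not support a direction.
- **Power.** Comparing 82.5% (at 0.48) with the planned 95%, a reader might infer that LOCF costs 12 points of power. It does not. The 95% assumes no missing data, and patients lost before Month 3 give a mixed model almost nothing. The fair comparator is completers: about 106 vs 41 at 0.6 gives 90%. With the planned baseline adjustment, simulated power for LOCF vs completers is 82% vs 90% at a baseline-outcome correlation of 0, 88% vs 92% at 0.3 and 95% vs 96% at 0.5. The dilution to 0.48 stands; most of the apparent power loss does not.
- **Standard error.** A reader might also infer that carrying values forward makes the standard error wrong. Each patient contributes one value. In simulation the model and empirical standard errors agreed (0.132 vs 0.131), and rejection was about 5% with no effect at any visit and equal dropout. The problem is bias.
- **Deaths.** The article does not say that scores are carried past death; its rule names dropouts. That reading is an inference from intention-to-treat plus LOCF plus mortality within the expected loss, and a full protocol may hold a separate rule.
- **Schedule.** The SF-36 shares a row with the EQ-5D in a table headed for the economic evaluation. Collection at every marked visit is the natural reading, but should be confirmed.

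**Conclusion.** The point holds as a weakness in the choice of primary analysis. LOCF is stated twice as the primary method for a single late endpoint with about 63 of 315 values expected missing, and it can bias the contrast either way. Under the assumptions shown, an extreme fading pattern gives 0.12 with about 11% rejection under no true one-year effect. Spread-out dropout gives about 0.06 with 8%. Loss before Month 3 turns 0.6 into about 0.48. Actual size and direction depend on trajectories and dropout patterns that the article does not give. An analysis of all visits removed the bias in every simulated scenario, but those scenarios were missing at random by construction. Severity is should-fix: the article acknowledges the issue in part, and the largest figures come from extreme cases.

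**What to change.** Make the primary analysis a mixed model for repeated measures on all scheduled SF-36 mental component z-scores from Month 3 to Month 15. Include visit, arm-by-visit, baseline and baseline-by-visit terms with unstructured covariance, and test the arm contrast at the one-year visit. Multiple imputation under missing at random, using the intermediate scores, is an acceptable alternative. Keep the hierarchical order of the two hypotheses.

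Move LOCF to the sensitivity analyses and add a reference-based imputation with TAU as the reference, to probe departures from missing at random.

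Treat deaths explicitly, because the article counts mortality in the expected loss and a mixed model does not resolve them: it implicitly models scores after death. Report deaths by arm and add a composite sensitivity analysis that ranks death as the worst outcome.

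The cost is a change of analysis wording and modest programming, made before unblinded analysis, with no new data on the natural reading of Table 1. The price is reliance on missing at random, which the reference-based analysis is there to test.
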